### 2.8. Management of acupuncture-related adverse events

The acupuncturist will take immediate action for adverse events related to acupuncture. In the event of minor adverse events such as localized bleeding and mild pain, the acupuncturist will apply pressure to the bleeding area to stop the bleeding and observe and reassure the painful area. In the event of a serious adverse event such as needle breakage or fainting, the patient will be quickly transported to the emergency room. Depending on the circumstances, the emergency room medical staff will take appropriate measures such as surgery, anti-infection treatment and emergency resuscitation to deal with the situation. Close monitoring of the patient’s condition and follow-up examinations will be conducted to ensure recovery.

### 2.9 Trial quality control, data management, and monitoring

Prior to the formal conduct of the trial, all study personnel will be issued with a workbook and receive standardized training to familiarize them with the implementation details of this study and to ensure consistency in the study execution process and the assessment of efficacy. They will learn uniformly how to interpret the eligibility criteria and complete the CRFs normatively. Acupuncturists will receive normative training in acupoint positioning and acupuncture operating procedures for COPD to ensure the safety of operation and effective blinding. RAs will exist and be trained independently to ensure complete randomization and allocation concealment. Clinical monitors will be set up to periodically verify that each investigator is strictly following the study protocol during the trial, and to periodically check the informed consent, inclusion and treatment progress of participants, as well as the completion of CRFs at each sub-center.

Raw clinical data will be collected by CRFs in paper version, entered and stored in a password-protected electronic database by specially trained data-entry personnel with unknown subgroups. Access to the database will be limited to specific researchers only. All paper copies of study documents will be stored centrally and locked. The Ethics Committee of the Affiliated Hospital of Chengdu University of Traditional Chinese Medicine may inspect the study records and monitor the trial.

### 2.10 Statistical analysis

Analyses of effectiveness, indicators of DNA library of gut microbiota, content of metabolites, percentage of immune cell and expression levels of inflammatory cytokines will be performed according to the Per Protocol Set (PPS) principle. The missing data will be filled in by multiple interpolation. SPSS 27.0 software (IBM Corp, New York) will be applied for statistical analysis. Quantitative indicators will be described by mean value (± standard deviation) or median (± interquartile range), and classification indicators by frequency and percentage. Baseline data will be analyzed using Chi-square or Fisher precision tests (data with frequency less than 5) and ANOVA. Sensitivity analyses will be performed using ANOVA.

The outcome of effectiveness, indicators of DNA library of gut microbiota, content of metabolites, percentage of immune cell and expression levels of inflammatory cytokines will be analyzed by linear mixed effects model. Fixed effects will be set for analyzing groups, COPD subtypes and smoking index (calculation method: smoking years × daily smoking number ÷20); Random effects for sub-centers and baseline outcome measures, both including intercept; Model-based covariance will be applied to test the fixed effects and coefficients, the degree of freedom will use residual method, and the maximum number of iterations will be set to 100. To control for type I error rates under multiple comparisons, the Benjamini–Hochberg method will be utilized for multiple comparison correction. Multiple linear regression will be used to analyze the relationship between clinical efficacy and gut microbiota, metabolites, immune cells and inflammatory factors. Statistical tests will be bilateral with *P* < 0.05 considered statistically significant.

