### 2.4 Sample size, randomization and blinding

#### 2.4.1 Sample size calculation

The primary outcome for this study is the change in the COPD Assessment Test (CAT) scores before (week 0) and after (week 12) the intervention. Sample size calculation is based on the results of our pilot trial, which showed a mean change in CAT scores of 5.0 for patients in the acupuncture group and 1.4 in the sham acupuncture group. Using a two-tailed test with type I error of 0.05 and power of 80%, a sample size of 32 cases per group is calculated with a maximum of 10% of participants allowed to drop out or disengage, for a required sample size of 36 cases per group, and a total of 72 participants will be included. Furthermore, 36 healthy participants will be included. The sample size calculation was completed in PASS 15.0 with One-Way Analysis of Variance (ANOVA) F-Tests module.

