##### 2.5.1.3 Basic treatment and medication changes

During the baseline period, all details of medications used by the patients to treat COPD and other underlying conditions will be recorded on a case report form (CRF), including the name of the medication, the dosage used, the frequency of use, the route of administration, and when the medications begin and end. Any changes in the patient’s medications throughout the study period will also be recorded in detail. If the patient experiences an acute exacerbation, the possibility of continuing acupuncture treatment will be assessed by a respiratory medicine specialist. If an acute exacerbation occurs that necessitates the application of antibiotics or hospitalization to control the infection, the trial will be discontinued and the time and reason for being discontinued will be recorded by the investigators.

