### 2.6 Outcome measurements

#### 2.6.1 Primary outcome

COPD Assessment Test (CAT) The change in the CAT scores before (week 0) and after (week 12) the intervention is chosen as the primary outcome.

The scale evaluates and reflects the severity of COPD patients’ conditions through 8 items, including 3 indicators of clinical symptoms: cough, sputum, and chest tightness, 2 indicators of tolerance: exercise tolerance, daily activities (status of limited activities at home), and 3 indicators of life quality: sleep quality, energy, and mood (confidence in outings). The response values of each item are ranging from 0 to 5 (0 = no impairment). Response values for all 8 items will be summed up to obtain the total scores of (ranging from 0 to 40). Higher scores indicate a greater impact of the disease on the patient’s health and life (46): 0–9 is considered a low impact, 10–20 is considered a moderate impact, 21–30 is considered a high impact, and 31–40 is considered a very high impact (47). In addition, week 4, week 8 and the follow-up period (week 38, week 64) will also collect data on this scale’s scores (Table 1).

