### 2.7 Safety assessment

Safety will be assessed by vital signs examination and routine blood tests before and after the treatment period. Adverse events (AEs) associated with the intervention, including bleeding, hematoma, needle breakage, local infection, persistent pain, syncope, etc., must be reported promptly and recorded in the CRFs, which included symptoms, signs, time of occurrence, extent, duration, disposal measures, process and results of AEs (Note: acute exacerbation of COPD is not counted as an adverse event). Serious cases should to be reported to the Project Management Office and Ethics Committee of Chengdu University of Traditional Chinese Medicine within 24 h and their participation in trial will be aborted. Upon occurrence of an adverse event, participants will immediately receive appropriate treatment and decide whether to withdraw from the trial at their own discretion. Participants who abort the trial will continue to be investigated and followed up, and the results will be recorded accordingly.

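### The Per Protocol Set is the only population named for effectiveness, including the primary CAT change, so the primary comparison depends on post-randomisation, outcome-related exits

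*Protocol article*

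**What the plan says.** All references are to the protocol article.

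- **Analysis set (section 2.10).** One sentence covers effectiveness, gut microbiota, metabolites, immune cells and cytokines; it ends "expression levels of inflammatory cytokines will be performed according to the Per Protocol Set (PPS) principle". No intention-to-treat, full analysis or other as-randomised set is named anywhere in the article, and the Per Protocol Set is not defined.
- **Primary outcome (section 2.6.1).** "The change in the CAT scores before (week 0) and after (week 12) the intervention is chosen as the primary outcome". It is an effectiveness outcome and so falls under that sentence.
- **Missing data and sensitivity (section 2.10).** "The missing data will be filled in by multiple interpolation", which I read as multiple imputation. Sensitivity analyses are to use ANOVA; no other population is mentioned.
- **Exit for exacerbation (section 2.5.1.3).** If an exacerbation calls for antibiotics or admission, "the trial will be discontinued and the time and reason for being discontinued will be recorded by the investigators".
- **Exit for serious adverse events (section 2.7).** Participation of serious cases is ended. The section then says: "Participants who abort the trial will continue to be investigated and followed up, and the results will be recorded accordingly". The same section does not count acute exacerbations as adverse events.
- **Sample size (section 2.4.1).** The pilot means for CAT change were 5.0 points with acupuncture and 1.4 with sham. At 80% power and a two-sided 5% level the article arrives at 32 per arm. Its only allowance for losses is worded "with a maximum of 10% of participants allowed to drop out or disengage", and this brings the number to 36 per arm.

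**The concern.** The trial asks whether real acupuncture is superior to sham. Randomisation supports that comparison only if patients are analysed in the arm to which they were allocated, whatever happened afterwards. The article instead commits the primary analysis to a set whose membership is decided after randomisation.

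The exits in this trial are related to outcome. Section 2.6.2.1 counts moderate or severe exacerbations in follow-up as a secondary outcome and defines them by much the same events (antibiotics and/or oral steroids, admission, emergency visit) that lead to discontinuation during treatment under section 2.5.1.3. The Discussion describes preventing exacerbations as a main purpose of treating stable patients. The primary comparison would therefore condition on something that acupuncture is meant to influence and that is likely to go with a poor CAT score.

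At stake is whether the primary estimate is a randomised comparison or one between selected patients. The ANOVA sensitivity analysis would not reveal the difference, because it names no other population.

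**Working it through.** **1. The plan's own figure.** Inflating 32 per group for 10% loss: 32 / 0.90 = 35.6, rounded up to 36 per group, 72 in total. This step reproduces. The 32 itself cannot be checked, because the article gives no SD.

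**2. Back-solved SD (an assumption).** The difference is 5.0 − 1.4 = 3.6 points. For a two-group comparison with two-sided alpha 0.05 and n per arm, power comes from the noncentral t distribution with 2n − 2 degrees of freedom and noncentrality 3.6 / (SD × √(2/n)). Setting n = 32 and power = 80% gives SD = 5.06. The power figures in steps 4 and 5 rest on this value.

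**3. Size of the gap between the two sets (illustration).** Suppose a share q of acupuncture patients stop treatment and change like sham patients, and the sham arm is unaffected. As randomised, the difference is (1 − q) × 5.0 + q × 1.4 − 1.4 = 3.6 × (1 − q). The Per Protocol Set still shows 3.6.

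| q | As randomised | Per protocol | Ratio of per protocol to as randomised |
|---|---|---|---|
| 10% | 3.24 | 3.6 | 1.11 |
| 20% | 2.88 | 3.6 | 1.25 |
| 30% | 2.52 | 3.6 | 1.43 |

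**4. Power in that same scenario (SD 5.06).** As randomised, 36 per arm with the diluted difference. Per protocol, 36 × (1 − q) against 36 with a difference of 3.6.

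| q | Power as randomised | Power per protocol |
|---|---|---|
| 10% | 76% | 83% |
| 20% | 66% | 80% |
| 30% | 55% | 77% |

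Here the as-randomised analysis has less power, so power is not a reason for the change.

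**5. Power of the Per Protocol Set if both arms lose patients alike.** The article gives no exit rate. Assume 0.5, 1.0 or 1.5 qualifying exacerbations per patient-year. The share with at least one in 12 weeks is 1 − exp(−rate × 12/52) = 11%, 21% or 29%. That leaves 32.1, 28.6 or 25.5 per arm, with power of 80%, 75% or 70%. At the low end the 10% allowance is roughly enough; a shortfall depends on the assumed rate.

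**6. Selection bias with no true effect (simulation, SD 5.02).** The patients who leave are those with the worst values of a latent variable correlated 0.3 to 0.5 with CAT change.

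- Exits 10% in each arm: bias about 0, type I error 5.0%.
- Exits 10% in one arm and 20% in the other: a spurious difference of about 0.25 to 0.40 points, type I error 5.4% to 6.1%.
- Exits 10% and 30%: 0.46 to 0.77 points, type I error 6.3% to 8.7%.

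The arm that loses more patients looks better, so the direction depends on which arm that is.

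**The case against.** The strongest reply has four parts.

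- **Exits may balance.** Patients and assessors are blinded and the exit rules are the same in both arms. With equal exit shares and mechanism the bias is about zero. This stands: the article gives no evidence that exits will differ by arm, and step 3 of the working is a one-sided illustration. It also reflects a difference between two estimands, since dilution from stopping treatment is real in the as-randomised effect. But balance cannot be known in advance, and not having to assume it is the reason for analysing as randomised.
- **The set is undefined, and the definition may be in an unseen document.** That discontinued patients leave the set is an inference from ordinary usage. A definition elsewhere could limit the damage, but the article positively names the efficacy population and names no other. This is a stated choice, not an omitted detail.
- **The change does not protect power.** Correct, as step 4 shows.
- **The data may not exist.** The follow-up sentence in section 2.7 sits among the adverse-event rules, which exclude exacerbations, and section 2.5.1.3 records only the time and reason of discontinuation. This stands too: the fix needs a clarification of follow-up as well as a new analysis set.

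A reader might also infer that patients who miss some of the 36 sessions are excluded, or that imputation would have almost nothing to fill. The article supports neither. Section 2.5.1 records expected and actual treatments to assess compliance but sets no threshold. Table 1 schedules CAT at six visits, so patients within the Per Protocol Set can still have missing assessments.

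**Conclusion.** The point holds. The article makes the Per Protocol Set the sole population for effectiveness in a superiority trial, while its exit rules act on post-randomisation events tied to prognosis. On the ordinary meaning of per protocol, the primary CAT comparison does not preserve randomisation, and no planned analysis would show how much that matters. It should be changed, because it governs the primary conclusion.

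The size is uncertain. Bias is about zero with matching exits and can go in either direction otherwise. Under the one-sided illustration the per-protocol difference of 3.6 points stands against 3.24, 2.88 or 2.52 as randomised, for 10%, 20% or 30% stopping. These figures rest on the pilot means and an assumed full return to the sham mean.

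Two stronger conclusions might be drawn and are not supported. One is that the plan is bound to favour acupuncture: nothing in the article shows which arm would lose more patients. The other is that the stated 80% power is lost under the Per Protocol Set and would be restored by the change. Any loss depends on exit rates that the article does not give, and under dilution the as-randomised analysis has the lower power.

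**What to change.** In section 2.10:

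- Make all randomised patients, in their allocated arm and with all collected CAT data whether or not treatment was stopped, the primary set for clinical effectiveness.
- Apply the multiple imputation already planned within that set.
- Keep the Per Protocol Set, with a definition, as a supportive analysis of the clinical outcomes and for the microbiome outcomes, where antibiotics act directly on the measurement.

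In sections 2.5.1.3 and 2.7, state that the continued outcome follow-up promised in section 2.7 also covers patients discontinued because of an exacerbation. This concerns data collection only; the clinical discontinuation rules are not in question here.

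**Cost.** Changes of wording in these sections and no extra patients. If follow-up after an exacerbation exit was not already intended, those patients need their remaining scheduled outcome assessments. The estimate may be smaller than the per-protocol one. If stopping treatment dilutes the effect, power with 36 per arm is about 76% at 10% dilution and 66% at 20% (back-solved SD 5.06), below the stated 80%. The sponsor should accept this openly or re-check the sample size against an expected exit rate.

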**Methods:**

This study is a multicenter randomized controlled trial. A total of 72 patients with stable COPD eligible will be randomized in a 1:1 ratio to receive either manual acupuncture (MA) or sham acupuncture (SA) without puncturing the skin. There will be no changes to the essential medicines used for all patients. The intervention will be 12 weeks, 3 times per week and follow-up will be 52 weeks. The primary outcome will be the change in COPD Assessment Test (CAT) score before and after treatment. Secondary outcomes will include modified Medical Research Council (mMRC), St. George’s Respiratory Questionnaire (SGRQ), 6-min walk test (6MWT), and the number of moderate or severe acute exacerbations during follow-up. A total of 36 healthy volunteers will also be recruited as normal control. In addition, feces and blood will be collected from each participant to characterize the gut microbiota, metabolomics, immune cells and inflammatory cytokines. Differences between COPD patients and healthy participants will be observed, as well as changes before and after treatment in MA and SA groups. Ultimately, the correlation among gut microbiota, metabolomics, immune cells, inflammatory cytokines and clinical efficacy in COPD patients will be analyzed.

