The gut microbiota and the metabolome are also important in the progression of COPD (26). Studies have shown that the fecal microbiome of COPD patients is different from that of healthy individuals (27). Streptococcus, streptococcus vestibularis, and lachnospiraceae are associated with reduced lung function (28). Human commensal bacteria can ferment dietary fiber into short-chain fatty acids (SCFA), which can activate immune cells via the NLRP3 inflammatory vesicle, affecting lung inflammation and promoting COPD progression (29, 30). Metabolomics analyses have revealed that abnormalities in amino acid metabolism, lipid metabolism, energy production, as well as oxidative and antioxidant abnormalities affect the pathogenesis of COPD (31, 32). Elevated serum levels of lysine, pyruvate, 3-hydroxybutyrate, and glutamine are strongly related to acute exacerbations in patients with COPD (33). Mammalian target of rapamycin (mTOR) is a critical enzyme body that regulates cell proliferation and metabolic processes. It has been found that certain metabolites can activate the mTOR pathway and promote the differentiation of Th17 cells, as well as bind to scaffolding proteins and regulatory proteins to form mTOR complexes, induce the expression of the hypoxia-inducible factor-1α (HIF-1α), and mediate the proteasomal degradation of the forkhead-box protein P3 (FOXP3, the key transcription factor in Treg cells) to inhibit the function of Treg cells (34). Evidence suggests that acupuncture may have a therapeutic effect on COPD by decreasing the levels of tumor necrosis factors-γ (TNF-γ) and IL-4 (35), which are related to the balance of the Th17/Treg pattern. Meanwhile, acupuncture has a certain regulatory effect on gut microbiota and metabolites (36, 37). However, there are no studies linking chronic inflammation, intestinal flora, and metabolomics to investigate the mechanism of acupuncture to improve COPD from a multi-omics perspective.

Therefore, a randomized, parallel-controlled and long-follow-up trial is designed to further validate the clinical efficacy of acupuncture as an adjunctive therapy for patients with COPD and to explore the relationship between clinical efficacy and gut microbiota, metabolome and inflammation.

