##### 2.6.2.2 Other indicators sent for testing

Fecal samples and fasting blood samples will be collected at baseline (week 0) and at the end of the intervention (week 12) for COPD patients, and only at baseline for healthy subjects.

(1) Changes in gut microbiota: The third generation of full-length 16S rRNA sequencing technology will be utilized to analyze the gut microbiota of participants.

Participants will be advised to maintain a normal diet (no specific changes from previous habits) and to avoid spicy, greasy or probiotic-containing foods such as yogurt prior to the collection of fecal samples. The sample should be collected approximately 4 g from the middle internal part of the feces using a disposable fecal kit and stored in a −80°C refrigerator within 30 min. The DNA of gut microbiota from fecal samples will be extracted by using dedicated kits, then a SMRT (single-molecule real-time) bell library will be constructed. SMRT sequencing will be performed on the PacBio Sequel II sequencing platform (Pacific Biosciences, USA). After raw data processing, clustering or noise reduction analyses will be performed to obtain ASVs (Amplicon Sequence Variants). Based on these sequences, species annotation, further cluster analysis and difference analysis can be performed. Indicators for the analysis of gut microbiota include structural diversity of the microbiota, and expression abundance of key strains as well as their intergroup differences.

(2) Changes in content of metabolomics: The untargeted metabolomics study will be performed on blood samples from participants by using liquid chromatography-tandem mass spectrometry (LC-MS/MS) technology (52, 53).

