Studies have shown that gut microbiota and metabolome dysregulation are strongly associated with the development and progression of COPD (66–68). Dysregulation of the gut microbiota leads to the production of a toxic substance lipopolysaccharide (LPS) (69). LPS can cross the intestinal barrier into the body circulation and reach the lungs, where it exacerbates COPD lung inflammation through the toll-like receptor 4/ nuclear transcription factor-κB (TLR4/ NF-κB) signaling pathway mediating the production of IL-1β, IL-6, IL-17 TNF-α (70). The transplantation of gut microbiota from healthy individuals can alleviate COPD-associated systemic inflammatory responses and lung histopathological damage (71). Pulmonary inflammatory mediators of COPD patients can cause elevated CRP (C-reactive protein) and keratinocyte-derived chemokines in peripheral serum, which subsequently disrupt intestinal immunity and homeostasis (72). Altered metabolism of phospholipid-derived sphingolipids and glycerophospholipids in COPD patients can lead to accumulation of ceramide in lung tissue, followed by dysregulation of endothelial defense mechanisms, induction of apoptosis in alveolar epithelial cells, promotion of inflammatory responses and macrophage dysfunction (73). Also, increased oxidative stress, phospholipid oxidation and activation of the innate immune system will contribute to the persistence of inflammation (74). Previous studies have investigated the modulation of the gut-brain axis by acupuncture using microbiomics and metabolomics approaches, providing meaningful evidence for the treatment of a wide range of disorders including stroke, insomnia, and Alzheimer’s disease (75, 76). Electroacupuncture has been proved to increase the levels of SCFA, a metabolite of gut microbiota in an ischemic stroke rat model, and attenuate brain and gut inflammatory injury in stroke rats by enhancing SCFA-mediated Foxp3 acetylation in Treg cells (77). However, there is a lack of studies in which acupuncture modulates the immune homeostasis of gut microbiota and lungs. The study will determine the pathological characteristics of the patients in terms of gut microbiota, metabolism and immune inflammation by comparing them with healthy volunteers and observe the modulating effect of acupuncture on these and explore their relationship with the efficacy of COPD.

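### The Per Protocol Set rule makes no exception for the week-0 COPD-versus-healthy comparison, so that contrast may be selected on later events; the effect is modest and its direction undocumented

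*Protocol article*

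**What the plan says.** Section 2.10 (Statistical analysis) sets one rule for effectiveness and all laboratory indicators: analyses of gut microbiota, metabolites, immune cells and "expression levels of inflammatory cytokines will be performed according to the Per Protocol Set (PPS) principle". The article does not define membership of that set. The next sentence reads "The missing data will be filled in by multiple interpolation". A later sentence in the same section reads "Baseline data will be analyzed using Chi-square or Fisher precision tests (data with frequency less than 5) and ANOVA"; it names no analysis set.

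A comparison with healthy people is planned. The Methods part of the abstract states: "Differences between COPD patients and healthy participants will be observed, as well as changes before and after treatment in MA and SA groups". The Discussion says that the disease characteristics of the patients will be determined "by comparing them with healthy volunteers". Section 2.6.2.2 schedules blood and fecal sampling at weeks 0 and 12 for patients "and only at baseline for healthy subjects", and Table 1 agrees.

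Patients can leave after week 0. Under section 2.5.1.3, if an exacerbation needs antibiotics or hospitalization, "the trial will be discontinued and the time and reason for being discontinued will be recorded by the investigators". Under section 2.7, participation is also ended for serious adverse events. Section 2.4.1 allows for at most 10% loss.

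**The concern.** Whether a week-0 sample is valid for describing COPD against health cannot depend on what the patient does or suffers in the following 12 weeks. A per-protocol condition is meant for a treatment comparison. Applied to the disease contrast, it filters the patient side on events after the sample was taken and leaves the volunteer side, which receives no treatment, unfiltered by any such event.

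The filter may not be neutral. Exits for exacerbation are foreseeable: Table 2 asks for at least one moderate or severe exacerbation in the past year (the list in the text of section 2.3.2.1 omits this item). The Introduction says that raised serum levels of four named metabolites "are strongly related to acute exacerbations in patients with COPD", and it links Th17/Treg imbalance to worsening disease. If patients who leave differ at week 0 from those who stay, the retained group no longer represents the COPD group that was enrolled. Usable samples, already collected, are also left out.

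**Working it through.** **Inputs from the article.** 72 COPD patients, 36 healthy volunteers, 32 evaluable per arm, and loss of at most 10% (section 2.4.1).

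**The plan's own figure.** 32/0.90 = 35.6, rounded up to 36 per arm, or 72 in total. This inflation step reproduces. The evaluable number is 2 × 32 = 64, so the plan allows for 8 losses. Because of rounding this is 8/72 = 11%; a literal 10% is 7.2 patients.

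**Assumptions, not in the article.** The difference *g* between excluded and retained patients at week 0, in SD units, positive when excluded patients lie further from healthy. Also any loss above the planned allowance, such as 25%.

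**Shift in the contrast.** Let *d* be the share excluded. The contrast in all patients is D_all = (1 − d) × D_kept + d × D_excluded, so D_kept − D_all = −d × g.

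| Excluded | g = +0.5 | g = +1.0 | g = 0 | g = −0.5 |
|---|---|---|---|---|
| 8 of 72 (plan's allowance) | −0.06 | −0.11 | 0 | +0.06 |
| 18 of 72 (25%, assumed) | −0.13 | −0.25 | 0 | +0.13 |

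For example, 8/72 × 0.5 = 0.056 and 8/72 × 1 = 0.111. At a literal 10% the first row is 0.05 and 0.10 in size.

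This formula needs *g* measured against the retained patients. If the excess is measured against the average of all 72, the multiplier is exits/(72 − exits). Then 8 exits give 8/64 × 0.5 = 0.06 to 8/64 × 1 = 0.13 SD, and 18 exits give 18/54 × 0.5 = 0.17 to 18/54 × 1 = 0.33 SD.

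**Standard error, in SD units.**
- All 72: √(1/72 + 1/36) = 0.204.
- 64 retained: √(1/64 + 1/36) = 0.208; ratio 1.021.
- 54 retained: √(1/54 + 1/36) = 0.215; ratio 1.054.

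**Power, as an illustration.** For an assumed true contrast of 0.6 SD (two-sided 0.05, no multiplicity correction), power is 84% with all 72 patients. With 10% excluded it is 82% if g = 0, 75% if g = +0.5 and 88% if g = −0.5. The last figure is higher only because the contrast is then overstated.

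With all week-0 samples used, the selection term is zero whatever *g* is.

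**The case against.** **The rule may not be meant for this comparison.** The indicators in the Per Protocol Set sentence recur almost word for word in the mixed-model sentence. That model has COPD subtype and baseline outcome as terms, which fit the treatment comparison and not volunteers sampled once. The baseline-data sentence names no set and might cover the disease contrast. This stands in part: use of the Per Protocol Set for the healthy comparison is the natural reading, but it is not explicit. Even so, the only sentence that assigns a set names exactly these markers and exempts nothing, and the same one-sentence change settles either reading.

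**The set is undefined, and definitions are commonly left to the analysis plan.** This is fair, and the missing definition is not the point here. The point is that the rule the article does state does not fit one of its planned comparisons.

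**Follow-up and imputation might deal with it.** Section 2.7 keeps following participants who stop, and multiple imputation is planned. Neither helps: the week-0 values concerned are observed, and they are lost because the analysis set excludes them.

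**A tempting stronger reading is that the rule understates the disease difference.** A reader might infer this from the Introduction. The article does not support it. No section says that patients who leave are further from healthy at week 0. The Introduction's statement covers four serum metabolites and does not say that levels in a stable patient predict a later exacerbation; it says nothing similar about microbiota. Exits for missed sessions, adverse events or other withdrawal could move the contrast either way or not at all.

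**Conclusion.** The point holds in a limited form. As written, a comparison that needs only week-0 samples is made to depend on treatment-period events, on the patient side alone. The bias has no documented direction; toward no difference is plausible for exits driven by exacerbations, and no more can be said. At the plan's allowance for loss it is modest: about 0.06 to 0.11 SD, with a standard error about 2% larger. The shift rests on an assumed 0.5 to 1 SD difference between excluded and retained patients, and on discontinued patients falling outside the undefined Per Protocol Set. The larger figures at 25% loss rest on a further assumption about loss. The comparison is secondary and mechanistic, and the primary CAT outcome is not affected by this point, so severity is minor.

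**What to change.** In section 2.10, limit the Per Protocol Set sentence to post-randomisation analyses. Add that the COPD-versus-healthy comparison uses every enrolled COPD patient with a valid week-0 sample (up to 72), whatever happens later, against the 36 healthy volunteers. The cost is one sentence. It needs no new samples, because the week-0 collection is already scheduled, and no change to patient care or to the number recruited.
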